### Data analysis

The data analysis will conform to a pre-specified statistical analysis plan. The analyses will start after collection of the 3-month follow-up data. There will be no interim analyses or stopping rules. Following the intention-to-treat analysis strategy, all analyses will include all participants with follow-up data in their groups as randomized, and sensitivity analyses will include all randomized participants to explore different assumptions about any missing data. Descriptive analyses will include summary tables (descriptive statistics and/or frequency tables) for baseline and follow-up variables as appropriate. A flowchart of recruitment of participants will be generated, including, e.g., the number of students screened and the number included in the primary and secondary analyses.

The binary outcomes of self-reported prolonged abstinence, 4-week prevalence of complete smoking cessation, and 7-day point prevalence of smoking abstinence will be analyzed by logistic regression and the results presented as odds ratios and 95% confidence intervals (CIs). Number of quit attempts and number of uses of other smoking cessation services will be analyzed by negative binomial regression and the results presented as ratios of means (95% CI). Number of cigarettes smoked weekly will be analyzed by logarithmic transformation and linear regression and the results presented as the ratio of geometric means (95% CI). All regression analyses will be adjusted for the following baseline variables: gender, duration of smoking, average number of cigarettes smoked weekly, severity of dependence as measured by Fagerström’s Nicotine Dependence Scale, and amount of snuff used at baseline. Effect modification analyses will be performed for the two primary outcomes and the following potential effect modifiers measured at baseline: gender, average number of cigarettes smoked weekly, amount of snuff used weekly, and severity of dependence. Each effect modification analysis will be performed by comparing adjusted logistic regression models, excluding and including the interaction parameter using the likelihood ratio test.

A sensitivity analysis will explore the effects of departures from the missing-at-random (MAR) assumption in the main analysis. We will use data on the number of follow-up texts and phone calls needed before an individual responded to explore the plausibility of the MAR assumption by exploring the association between quitting and the number of follow-up attempts needed.

All tests will be performed two-sided with a 5% level of significance.

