### Participants and procedure

Participants will be recruited through advertisements in high schools in Sweden. High school in Sweden is a free and voluntary level of education after primary school. The majority of pupils attending high school in Sweden are between 16 and 19 years of age. Inclusion criteria will be high-school pupils who are daily or weekly smokers, are willing to attempt to quit smoking, and own a mobile phone. A flowchart of the recruitment procedure for the study is presented in Fig. 1 and a Standard Protocol Items: Recommendations for Interventional Trials (SPIRIT) Figure is presented in Fig. 2.

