### Baseline questionnaire

The baseline questionnaire will include a total of 14 items investigating (1) number of year(s) of smoking, (2) frequency of using snuff, (3–8) Fagerström’s Nicotine Dependence Scale, (9) readiness to quit within the next 4 weeks, (10) number of previous quit attempts, (11) previous use of other smoking cessation aids, (12) previous support from smoking cessation specialist, (13) how they found out about the program, and (14) gender.

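### The quit-attempt and service-use models leave out the related prior behaviour already collected at baseline; the plan is valid but may forgo some efficiency

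*Protocol article*

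**What the plan says.** The Data analysis section gives one adjustment set and applies it to all outcomes: "All regression analyses will be adjusted for the following baseline variables: gender, duration of smoking", then "average number of cigarettes smoked weekly, severity of dependence as measured by Fagerström’s Nicotine Dependence Scale, and amount of snuff used at baseline". That makes five covariates.

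The Baseline questionnaire section lists 14 items. Among them are "9) readiness to quit within the next 4 weeks, (10) number of previous quit attempts, (11) previous use of other smoking cessation aids" and "12) previous support from smoking cessation specialist". None of these four items (9 to 12) is in the adjustment set, and none is among the listed effect modifiers. No reason is given.

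The two secondary outcomes nearest to items 10 to 12 are counts: "Number of quit attempts and number of uses of other smoking cessation services will be analyzed by negative binomial regression". The abstinence outcomes use logistic regression with odds ratios.

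**The concern.** The plan treats its own outcomes unevenly. Weekly cigarettes at follow-up is modelled with baseline weekly cigarettes as a covariate. Quit attempts and service use are modelled without the earlier quit attempts, aids and specialist support that every participant reports before randomisation. Three of the five chosen covariates describe smoking exposure or dependence (duration, weekly cigarettes, Fagerström score), and none describes motivation or quit history.

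Prior behaviour of the same kind is often a good predictor of later behaviour. If it is here, the two count models will give less precise treatment ratios than the collected data allow. What is at stake is efficiency, mainly for secondary outcomes. Validity is not in question.

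**Working it through.** **Inputs from the protocol article.** Abstinence of 25.9% and 14.6%, 195 evaluable per group, 30% attrition and 279 per group (Power calculation); the five covariates and model types (Data analysis); items 9 to 12 (Baseline questionnaire).

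**The plan's own figure.** The uncorrected unpooled formula gives n = (1.960 + 0.842)² × (0.259 × 0.741 + 0.146 × 0.854) / 0.113² = 194.6, so 195; and 195 / 0.7 = 278.6, so 279. With the continuity correction that the text mentions, the result is 212 (unpooled) or 215 (pooled). That discrepancy is a separate matter: 195 serves here only as the evaluable group size.

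**Assumptions.** The predictive strength of items 9 to 12 is not in the documents, so a range is used. The simulations compare a model with treatment only against one with treatment plus one prognostic score. They carry over to this trial only if the strength is read as what an item adds beyond the five planned covariates.

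**Count outcomes.** Negative binomial regression, 195 per arm, assumed control mean 2, residual dispersion 0.7, true rate ratio 1.3, 300 simulated trials per row. The variance ratio is (SE with item / SE without)².

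| Rate ratio per SD | SE without | SE with | Variance ratio | Variance reduction |
|---|---|---|---|---|
| 1.0 | 0.1082 | 0.1083 | 1.00 | none |
| 1.2 | 0.1100 | 0.1085 | 0.97 | 3% |
| 1.4 | 0.1143 | 0.1094 | 0.92 | 8% |
| 1.6 | 0.1199 | 0.1106 | 0.85 | 15% |
| 2.0 | 0.1331 | 0.1142 | 0.74 | 26% |

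**Abstinence outcomes.** Logistic regression, 195 per arm, marginal rates held at 14.6% and 25.9%, 3,000 simulated trials per row. The marginal log odds ratio is ln[(0.259/0.741)/(0.146/0.854)] = 0.715.

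| Odds ratio per SD | Conditional log OR | SE without | SE with | Power without | Power with |
|---|---|---|---|---|---|
| 1.0 | 0.715 | 0.263 | 0.264 | 80.2% | 79.8% |
| 1.25 | 0.721 | 0.263 | 0.265 | 79.2% | 79.5% |
| 1.5 | 0.734 | 0.263 | 0.268 | 80.2% | 81.3% |
| 2.0 | 0.769 | 0.263 | 0.274 | 80.3% | 82.7% |
| 2.5 | 0.808 | 0.263 | 0.281 | 78.2% | 83.4% |

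The standard error rises with adjustment, so the interval for the log odds ratio does not narrow. Power rises because the conditional log odds ratio moves further from zero than the standard error grows: 0.715/0.263 = 2.72 without the score, 0.769/0.274 = 2.81 with it at an odds ratio of 2.0. The true power without the score is the same in every row, so its spread (78.2% to 80.3%) is simulation noise, and differences of a point or so should be read with that in mind.

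**Cost in model size.** Expected abstainers: 195 × 0.259 + 195 × 0.146 = 50.5 + 28.5 = 79. Treatment plus five covariates, each counted as one parameter, gives 79/6 = 13 events per parameter. Adding readiness alone gives 79/7 = 11. Adding all four items would give 79/10 = 8.

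**The case against.** The strongest reply is that a pre-specified five-covariate set is valid under randomisation whichever predictors it contains, so choosing others is a matter of preference. This stands: nothing is misstated or contradicted.

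Several stronger readings are tempting, and the documents do not support them:

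- A reader might infer that precision is wasted as a matter of fact. The documents give no predictive strength, and the gain is nil if the items add nothing to the existing set.
- A reader might infer that the primary odds ratios will have wider intervals than necessary. For a logistic odds ratio the opposite happens; only power gains, and modestly.
- A reader might take the simulated gains as gains over the plan. The simulated comparator is unadjusted, while the plan already adjusts for five variables, so the increment could be smaller than an item's raw association suggests.
- A reader might call items 10 to 12 the baseline values of the outcomes. They are prior history, whereas the outcomes count events since enrolment or first invitation. Aids and specialist support are also not the same measure as number of uses of other services.
- A reader might infer that chance imbalance under simple randomisation invalidates the primary result. The interval and type I error already allow for it.
- Because "all analyses will include all participants with follow-up data in their groups as randomized", a reader might infer that the omission undermines the missing-at-random assumption. The documents do not show that these items predict response.

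Eligibility also limits readiness as a predictor, since participants must be "daily or weekly smokers, are willing to attempt to quit smoking, and own a mobile phone". Item 9 asks about the next 4 weeks, so it can still vary, but the higher assumed odds ratios become less plausible.

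One defence does not stand: that covariate choice is left to the separate statistical analysis plan. The article itself closes the list for all regressions, so the choice is made there.

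**Conclusion.** A minor, optional improvement. The omission of items 9 to 12 from every model is certain from the text; the size of the loss is not. For quit attempts and service use, the variance of the treatment log rate ratio would fall by about 3 to 26% at rate ratios of 1.2 to 2.0 per SD, and not at all if the items are uninformative given the five covariates. These figures also rest on the assumed mean, dispersion and treatment effect. For the abstinence outcomes, adding readiness is worth about 0 to 2 points of power up to an odds ratio of 2.0 per SD. The case is best for the two secondary count models and weak for the primary outcomes.

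**What to change.** Before any 3-month outcome data are seen, amend the covariate sentence in Data analysis (and the statistical analysis plan to match):

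- keep the five common covariates for all models;
- add number of previous quit attempts (item 10) to the quit-attempts model;
- add previous use of cessation aids and previous specialist support (items 11 and 12) to the service-use model;
- optionally, add readiness to quit (item 9) to the abstinence models, stating that the aim is a small power gain and that the odds ratio is conditional on the covariates.

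Items 10 to 12 should stay out of the abstinence models, to limit the parameter count. The cost is a sentence or two of text. No new data are needed, and because the baseline questionnaire is completed before randomisation, no participants should be lost. In the prolonged-abstinence model, readiness takes one more parameter, about 11 rather than 13 events each.

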### Aim and hypotheses

The study aims to evaluate the effectiveness of a newly developed mHealth intervention targeting smoking among high-school pupils. The primary hypothesis is that participants in the intervention group will report significantly higher cessation rates (measured by the primary outcome measures) at follow-up compared with participants in the control group. Secondary hypotheses are that the intervention group will report significantly higher rates of 7-day point prevalence of smoking abstinence, higher mean number of quit attempts since taking part in the study, fewer number of uses of other smoking cessation services since first invitation to the study, and lower numbers of cigarettes smoked weekly if still smoking at follow-up, compared with the control group. These hypotheses are proposed at 3, 6, and 12 months’ follow-up.

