### Outcome measures

Outcome measures will be investigated via questionnaires at baseline and at 3, 6, and 12 months after enrollment. The primary outcomes will be: (1) prolonged abstinence (not smoked more than five cigarettes in the last 8 weeks) and (2) 4-week point prevalence of smoking abstinence. Secondary outcomes will be: (3) 7-day point prevalence of smoking abstinence; (4) mean number of quit attempts since taking part in the study; (5) number of uses of other smoking cessation services since first invitation to the study, e.g., calling help line; and (6) number of cigarettes smoked weekly if still smoking.

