**Fig. 2 Fig2:**
[figure not shown]
Standard Protocol Items: Recommendations for Interventional Trials (SPIRIT) Figure

School principals will be contacted via e-mail and invited to take part in the study. Recruitment will last for 6 months and be executed by paper advertising (posters and leaflets), digital advertising (e-mail, school website, or app if applicable), and by school staff (teachers, mentors, and/or school health centers). Pupils will register their interest by sending a text message to a dedicated telephone number (included in all information materials). Informed consent and the baseline questionnaire will be completed on their mobile phone. After completing the baseline questionnaire, participants will immediately be randomized to the intervention group or the control group. A text message will be sent to each participant to inform them to which group they have allocated.

All participants will be sent a follow-up questionnaire via a text message (with a link to the questionnaire) at 3, 6, and 12 months after enrollment (3-month interval will be primary outcome). Three reminders, 2 days apart, will be sent to non-responders, also via text message. In addition, participants who still do not respond will be telephoned every second day, with a maximum of three phone calls. These phone calls will only include two questions investigating the primary outcomes (prolonged abstinence and 4-week point prevalence of smoking abstinence).

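### Two primary outcomes at 3 months are each tested at an unadjusted 5%, with no statement of whether one or both must succeed, and the primary time point is not stated consistently

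*Protocol article*

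**What the plan says.** All places are in the Methods of the protocol article.

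- **Outcome measures** lists two primary outcomes on an equal footing: "The primary outcomes will be: (1) prolonged abstinence (not smoked more than five cigarettes in the last 8 weeks) and (2) 4-week point prevalence". The Abstract names the same two, and Data analysis speaks of two primary outcomes when it sets out the effect-modification analyses.
- **Aim and hypotheses** states one primary hypothesis over both: "participants in the intervention group will report significantly higher cessation rates (measured by the primary outcome measures) at follow-up compared with participants in the control" arm. After the secondary hypotheses it adds: "These hypotheses are proposed at 3, 6, and 12 months’ follow-up".
- **Participants and procedure**, in a parenthesis on the follow-up questionnaires: "3-month interval will be primary outcome".
- **Power calculation** sizes the trial on prolonged abstinence alone (25.9% v 14.6%, 80% power, two-sided 0.05): 195 evaluable per group, and 279 per group with 30% attrition.
- **Data analysis** gives one level for all tests: "All tests will be performed two-sided with a 5% level of significance". The same section says: "There will be no interim analyses or stopping rules". Looks at accumulating data are therefore not part of this point.

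Data analysis also refers to a pre-specified analysis plan, which is not shown.

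**The concern.** A single primary hypothesis measured by two outcomes can be read in two ways. Under one reading, a significant result on either outcome confirms it. Under the other, both must be significant. With each test fixed at 5%, the first reading does not hold the error at 5%. The second does, but it makes success depend on an outcome for which the trial was not sized.

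The choice matters because the earlier trial's own figures make a split result likely, with one outcome significant and the other not. The protocol then gives no basis for calling the trial positive or negative, and a decision made after seeing the data would be open to challenge.

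The time point adds a second ambiguity. One section makes 3 months primary. Another proposes the hypotheses, the primary one included, at all three follow-ups without ranking them.

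**Working it through.** **1. The plan's own figure.** Unpooled normal formula, two-sided 0.05, 80% power:

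n = (1.960 + 0.842)² × [0.259×0.741 + 0.146×0.854] / (0.259 − 0.146)² = 7.849 × 0.3166 / 0.01277 ≈ 194.6, so 195 per group.

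With 30% attrition, 195 / 0.70 = 278.6, so 279 per group and 558 in total. The printed 195 thus comes out without a continuity correction. With the correction that the section mentions, the calculation gives 215. That is a separate matter and does not affect the argument here. The calculation spends the full 0.05 on prolonged abstinence.

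**2. Error at 3 months if either outcome suffices.** Let Z₁ and Z₂ be the two test statistics, standard normal with correlation r when there is no effect. The error is P(|Z₁| > 1.96 or |Z₂| > 1.96). For r = 0 this is 1 − 0.95² = 9.75%. For r > 0 it comes from the bivariate normal distribution. The documents give no r, so the range is shown. The last column counts only errors in favour of the intervention, against a nominal 2.5% for one test.

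| Assumed r | At least one false positive | In favour of the intervention only |
|---|---|---|
| 0 | 9.75% | 4.9% |
| 0.5 | 9.1% | 4.5% |
| 0.7 | 8.3% | 4.2% |
| 0.8 | 7.8% | 3.9% |
| 0.9 | 7.0% | 3.5% |

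The outcomes overlap strongly (8 weeks with at most five cigarettes, and abstinence over 4 weeks), so the lower rows are plausible.

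**3. Error and power if both are required.** The error cannot exceed that of either test alone, so it is at most 5%. Power with 195 evaluable per group, at the earlier trial's rates (Background and Power calculation), by the same unpooled formula without covariate adjustment:

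- Prolonged abstinence, 25.9% v 14.6%: standard error √(0.3166/195) = 0.0403; 0.113/0.0403 = 2.80; power Φ(2.80 − 1.96) = 80%.
- 4-week point prevalence, 20.6% v 14.2%: standard error √[(0.1636 + 0.1218)/195] = 0.0383; 0.064/0.0383 = 1.67; power Φ(1.67 − 1.96) = 39%.

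The power to win on both is 36% at r = 0.5 and 38% at r = 0.8, and it cannot exceed 39%. The chance that exactly one is significant is 80% + 39% − 2 × (36% to 38%), about 42% to 47%.

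**4. If later visits could also carry the primary claim.** This gives six tests (2 outcomes × 3 visits). Independent tests give 1 − 0.95⁶ = 26.5%. For correlated statistics, a simulation of 400,000 draws from a six-variate normal distribution gave the following (all correlations assumed):

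| r between outcomes | r between visits | At least one false positive |
|---|---|---|
| 0.5 | 0.5 | 21.9% |
| 0.6 | 0.6 | 20.1% |
| 0.7 | 0.7 | 17.7% |
| 0.8 | 0.8 | 15.0% |
| 0.9 | 0.8 | 13.5% |

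**The case against.** The strongest reply is that an article condenses the full plan, and a hierarchy or success rule is something the unseen analysis plan may hold. That has force: the absence of a rule is not in itself a fault. What stands is what the article does state, namely two outcomes labelled primary, one hypothesis over both, and 5% for every test. An analysis plan that used a reduced level would contradict that last sentence. The number of primary outcomes and the primary time point belong to the protocol.

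A second reply is that the plural wording of the hypothesis may mean that both outcomes are required, in which case 5% is held. This also stands as far as it goes. A reader might infer that the false-positive rate simply is 8% or 9%, but the text does not say that either result suffices, so the figure is conditional.

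A third reply concerns time points. A reader might infer a false-positive rate near 20%, counting six primary tests. The document does not support this as its plan. Participants and procedure makes 3 months primary, and the Discussion describes 6 and 12 months as the intermediate and long-term effects. The sentence in Aim and hypotheses does not say that a later visit can confirm the primary hypothesis. It does sit badly with the 3-month designation, and the two need one wording.

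Finally, a fixed sequence is not the only cure. Requiring both outcomes, or splitting alpha, would also control the error, at the costs set out under the fix.

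**Conclusion.** The point holds for the 3-month pair. The protocol fixes two primary tests at an unadjusted two-sided 5% and leaves open whether one or both must succeed. If either suffices, the family-wise error is about 7% to 9.75% (assumed correlation 0.9 down to 0). If both are required, it is at most 5%, with power of no more than about 39%, assuming the earlier trial's rates and 195 evaluable pupils per group.

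The three-visit wording is a conflict to reconcile, not evidence of a larger error rate. Only if 6- and 12-month results could carry the primary claim would the error rise further, to about 13% to 26%, again on assumed correlations.

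This should be fixed. The repair is one of wording, and the excess at the designated time point is about 2 to 5 percentage points under one of two readings.

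**What to change.** - In Outcome measures and Data analysis, name prolonged abstinence at 3 months as the single primary test, at two-sided 5%. The sample size was computed for this outcome at this level, so the primary test needs no alpha reduction and no more pupils.
- Test 4-week point prevalence at 3 months, also at 5%, only if the first test is significant (fixed sequence).
- State that all 6- and 12-month tests are secondary, and reword the last sentence of Aim and hypotheses to agree with the 3-month designation in Participants and procedure.
- Qualify the sentence that sets 5% for all tests so that it refers to this order.

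The cost is that 4-week point prevalence alone can no longer carry the trial.

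The alternatives cost more. Splitting alpha at 0.025 each needs (2.241 + 0.842)² × 0.3166 / 0.01277 ≈ 236 evaluable per group for prolonged abstinence (236 / 0.70, so 338 per group with 30% attrition, 676 in total). Keeping 195 leaves about 71% power. Requiring both outcomes leaves at most about 39%.

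Trial status says the trial had not started at submission, so on that footing the choice could be fixed before any outcome data existed.

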## Discussion

All high schools in Sweden are bound by law to offer a smoke-free environment for their pupils. However, little effort has gone into finding effective ways of systematically helping pupils who wish to quit smoking; the emphasis is on the prevention of uptake. Following the success of our NEXit smoking cessation trial among university students, we believe that a similar mHealth intervention targeting high-school pupils may also be effective. The potential direct benefit from the trial is an intervention program that can be made available nationwide at very low cost, requiring little or no resources from participating high schools.

Although smoking cessation programs delivered via text messages have been evaluated previously, there has not been much research on the medium- and long-term effects of the intervention. The current research project, therefore, investigates not only the immediate effect at 3 months but also the intermediate and long-term effects at 6 and 12 months.

A limitation of the study is that follow-up will not be biochemically verified, but will rather rely on participants’ self-reported abstinence. However, any bias in reporting may be assumed to be equal in both the intervention group and the control group. Also, The Society for Research on Nicotine and Tobacco recommends that, in population-based studies with limited face-to-face contact, it is neither required nor desirable to use biochemical verification [22].

